#### Lifestyle.

Physical activity [88], sleep quality [84], adherence to the Mediterranean diet [89], dietary intake [90], and gut health [91] will be assessed as lifestyle-related variables. Detailed descriptions of these measures are provided in Table 2.

#### Physical and physiological measures.

Anthropometric characteristics, including height, weight, and waist and hip circumferences, will be assessed following the procedures recommended by the International Society for the Advancement of Kinanthropometry (ISAK). Body Mass Index (BMI) will be calculated from height and weight measurements and Waist-to-Hip Ratio (WHR) will be calculated from waist and hip circumference [92]. The assessment will also include physical fitness components such as aerobic capacity [93], balance [94], flexibility [95], handgrip strength [96], and lower body muscle power [97]. Physiological stress will be examined through HRV, analyzed using the root mean square of successive differences (RMSSD) method [98], along with measurements of systolic and diastolic blood pressure in millimeters of mercury (mmHg) [99]. A detailed overview of all assessments is provided in Table 2.

#### Biological measure.

Stool samples will be collected using the DANASTOOL Sample Collection MICROBIOME Kit (Danagen-Bioted, BCN, Spain). Participants will receive instructions and will be asked to collect stool from 2–3 different spots using the attached spoon, then transfer the sample into the stabilizing liquid in the tube to preserve microbial DNA. After the sample is added, the tube will be shaken to ensure homogenization. Each tube will be labeled with the participant’s code and collection date before being sent to the laboratory at room temperature (15–25 °C) for analysis. Microbial DNA will be extracted from a 0.5–1.0 g stool sample using the DANAGENE MICROBIOME Fecal DNA Kit, following the manufacturer’s protocol [100]. The microbial composition will be assessed through 16S *rRNA* gene-targeted sequencing. The sequencing data will then be processed and analyzed using the ZymoBIOMICS Service: Targeted Metagenomic Sequencing (Zymo Research, Irvine, CA). To complement taxonomic profiling, we will conduct a functional prediction analysis of the gut microbiota using *Phylogenetic Investigation of Communities by Reconstruction of Unobserved States,* version 2 (PICRUSt2) [101]. This tool infers the potential metabolic functions of microbial communities based on 16S *rRNA* gene sequencing data and reference genome databases. After quality control and OTU/ASV assignment, functional profiles will be predicted in terms of gene family abundance (e.g., KEGG Orthologs) and metabolic pathways (e.g., KEGG pathways, MetaCyc).

#### Usability and feasibility of VR interventions.

The quantitative assessment of the VR system’s usability will be conducted using the System Usability Scale (SUS), with scores ranging from 0 to 100, where higher scores indicate greater usability [102]. The feasibility of the VR program will be assessed through the following: (1) Measuring engagement levels, based on adherence rates, including session attendance and time spent in VR; (2) Evaluating program acceptability by collecting participant feedback through structured interviews, guided by the Unified Theory of Acceptance and Use of Technology (UTAUT), to better understand their experience with the VR intervention; (3) Analyzing effectiveness, using outcome measures relevant to the study objectives.

#### Perceived outcomes and qualitative interviews.

Participants will complete an expectation questionnaire to assess their perceived treatment effects on cognition, emotional well-being, physical fitness, and quality of life resulting from the study interventions. A purposive subsample of twelve participants from each study will also be invited to participate in a semi-structured interview to explore their experiences with the intervention and their perceptions of its impact (see S5 File). These interviews will examine perceived benefits, barriers, and contextual factors that influenced participant engagement and adherence, such as motivation and environmental influences. Participants will also be encouraged to reflect on their overall experience and offer recommendations for improving future interventions. All interviews will be audio-recorded and transcribed verbatim, and the transcripts will undergo participant validation to enhance accuracy and completeness. All data will be securely stored on a password-protected institutional server, in accordance with institutional data protection and retention policies. Furthermore, documentation will be maintained throughout the data collection phase to enhance transparency and consistency [103]. The qualitative data will be integrated with the quantitative findings using a complementary mixed-methods approach to provide a more comprehensive understanding of the intervention’s effects [104].

### Statistical analyses

Data will be entered into a version-controlled Excel database. Analyses will be conducted using the latest available versions of IBM SPSS Statistics and R. A two-tailed p-value < 0.05 will denote statistical significance, with adjustments for multiple comparisons applied where appropriate. Descriptive statistics (means, standard deviations, medians, ranges, and frequencies) will summarize baseline characteristics overall and by group. We will assess distributional assumptions, including skewness and the presence of outliers. Missing data will be characterized by reporting the percentage of missing values for each variable and by evaluating the most likely mechanisms, classified as missing completely at random (MCAR), missing at random (MAR), or missing not at random (MNAR).

Primary hypotheses will be tested under an intention-to-treat (ITT) framework, including all randomized participants. Analysis of covariance (ANCOVA) will model change scores (post-intervention – baseline) using group, baseline score, and selected covariates as predictors. Sex and age will be included as covariates in all analyses. Additional covariates will be considered from a pool of theoretically relevant candidates if they show a significant and meaningful association with the outcomes. To minimize multicollinearity, we will examine the interrelationships among selected predictors and retain only one variable when substantial overlap is observed. If the omnibus test is significant, we will perform pairwise comparisons within each outcome variable using appropriate corrections for multiple comparisons (e.g., Bonferroni). Assumptions of homogeneity of regression slopes, normality, and homoscedasticity of residuals will be checked. If violated, alternative models (e.g., mixed-effects models for repeated measures) will be considered. Between-group findings will be supplemented by within-group analyses (paired t-tests or Wilcoxon tests, as appropriate).

Missing outcome data will be handled using multiple imputation by chained equations (MICE), assuming data are MAR. Predictive mean matching will be applied, with the number of imputations and iterations guided by current recommendations [105]. The imputation model will mirror ANCOVA predictors and include auxiliary variables to improve accuracy. We will assess imputation diagnostics (trace plots, distributional comparisons) and pool results using Rubin’s rules. Complete-case analyses and sensitivity tests under MNAR will also be reported. Exploratory analyses will examine adherence as a continuous predictor and test adherence-by-treatment interactions. These models will include the same set of covariates used in the primary ANCOVA analyses to ensure comparability. Mediation and moderation effects will be tested using Hayes’s PROCESS macro with a minimum of 5,000 bootstrap samples. Given the proof-of-concept nature of Study 2, effect sizes (partial eta squared for ANCOVA) will be reported to aid interpretation of the findings.

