**Methods:**

Two mixed-methods randomized controlled trials will be conducted. In Study 1, participants will be randomly assigned to one of three groups (HIFT, MBSR, QG) using a 1:1:1 ratio. Psychological, cognitive, physical, physiological, and biological measures will be evaluated two weeks before and after the interventions. The interventions include three weekly sessions for 12 weeks. Subsequently, a follow-up will be conducted 12 weeks after the intervention to assess psychological well-being. Study 2 is a proof-of-concept study in which VR interventions will be co-designed with input from university students and professionals. Twelve participants from each study will also complete semi-structured interviews to explore their experiences and perceived impact.

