### Randomization

In Study 1, an independent researcher will use a software-generated random sequence to allocate participants into three groups at a 1:1:1 ratio for each wave (Fig 3). The randomization list will be securely generated and stored on a university server. While the research team will be aware of the allocation sequence, participants will remain unaware of their group assignment until the intervention. In Study 2, participants will be assigned to one of three intervention groups through sequential cohort assignment based on recruitment order. Potential biases in group composition will be mitigated by monitoring baseline characteristics across groups and adjusting for these in subsequent analyses. Outcome assessors will be blinded to group allocation through the use of coded identifiers to ensure unbiased assessments. To prevent unintentional disclosure, participants will be reminded not to discuss their group allocation during post-intervention assessments. To assess blinding success, outcome assessors will guess participants’ group assignments after the final evaluation. The proportion of correct guesses will be compared to the 33% chance level using a chi-square goodness-of-fit test with one degree of freedom. Data analysts will conduct analyses without access to group allocation information, thereby ensuring the integrity of the results.

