### Sample size

A power analysis was conducted using G*Power software (version 3.1.9.4) for a one-way ANOVA (fixed effects, omnibus) with three groups. Assuming a medium effect size (f = 0.25), α = 0.05, and a desired power of 0.80, the analysis yielded a required sample size of 159 participants, with a critical F-value of 3.054. To accommodate an expected dropout rate of 10%, the sample size was adjusted using the proportional method, resulting in a final target of 177 participants (59 per group). This adjustment ensures that statistical power remains adequate even if participant attrition occurs. Study 2 will include 45 participants (n = 15 per group) as part of a proof-of-concept trial intended for preliminary exploration. For Study 1, biological samples (fecal) will be collected from a randomly selected subgroup of 90 participants (30 per group) before and after the interventions. Furthermore, a subset of 24 participants (12 from each study) will be selected for the qualitative study using purposive sampling to capture diverse perspectives [67]. The sample size is based on previous studies [56,61,68] and evidence suggesting that qualitative inquiry often reaches data saturation with approximately 12 participants [69].

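### With three arms, correcting the pairwise tests again after a significant omnibus test is valid but needlessly conservative

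*Protocol article*

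**What the plan says.** Study 1 compares exactly three arms. The abstract says that "participants will be randomly assigned to one of three groups (HIFT, MBSR, QG) using a 1:1:1 ratio", and the Randomization section repeats the ratio within each recruitment wave.

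The Statistical analyses section sets the general level: "A two-tailed p-value < 0.05 will denote statistical significance, with adjustments for multiple comparisons applied where appropriate". For the ANCOVA on change scores it then sets two steps within each outcome: "If the omnibus test is significant, we will perform pairwise comparisons within each outcome variable using appropriate corrections for multiple comparisons (e.g., Bonferroni". The first step is the omnibus gate. The second is a further correction of the pairwise tests. Bonferroni is the only method named, and it is named as an example.

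The Sample size section powers only the first step. The calculation is "for a one-way ANOVA (fixed effects, omnibus) with three groups", and makes no separate allowance for corrected pairwise tests.

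**The concern.** The omnibus test can show that the three programmes are not all alike. It cannot show which one is better. Study 1 has no inactive control, and its between-group hypotheses (Objectives and hypotheses) are about ranking: HIFT ahead on cognition, MBSR ahead on psychological outcomes, and QG moderate on both. Only the pairwise contrasts can test that.

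Those contrasts have to pass two hurdles. With four or more arms a second hurdle of some kind would be needed, because an omnibus gate alone does not protect every subset of arms. With three arms the gate is enough to hold 5% within an outcome. A further correction then takes power from the comparisons of most interest without being needed for the nominal level.

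**Working it through.** **1. The plan's own figure.** Inputs from the Sample size section: three groups, f = 0.25, α = 0.05, power 0.80, stated total 159 with critical F 3.054, and 10% dropout.
- Noncentrality: λ = N·f² = 159 × 0.0625 = 9.94, on 2 and 156 degrees of freedom.
- Critical F = 3.0540 and power = 0.805. The smallest total reaching 0.80 is 158, and equal groups make it 159, or 53 per arm.
- Dropout: 159 / 0.90 = 176.7, rounded up to 177 = 3 × 59.

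The plan's figures reproduce.

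**2. Why the gate suffices with three arms.** The pairwise nulls are A = B, A = C and B = C. If any two hold, so does the third. The possible cases are therefore:
- All three nulls true. Any false claim must first pass the omnibus test, so its probability is at most 0.05.
- Exactly one null true. The only possible false claim is on that pair, whose own test is at 0.05, so its probability is again at most 0.05.
- None true. No false claim of a difference is possible.

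This is a closed test with strong family-wise control within one outcome.

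**3. What Bonferroni changes.** With 156 degrees of freedom the two-sided critical t is 1.975 at 0.05 and 2.420 at 0.05/3. The standard error of a difference, in SD units, is √(2/53) = 0.194. The smallest observed difference that is significant rises from 1.975 × 0.194 = 0.38 SD to 2.420 × 0.194 = 0.47 SD.

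**4. Simulation.** There were 400,000 trials per scenario, with normal data, 53 per arm, pooled variance and all pairwise tests gated by the omnibus F. Patterns of means at f = 0.25:
- Evenly spaced: extreme difference d = 2f/√(2/3) = 0.61 SD, adjacent difference 0.31 SD.
- One arm different: d = 3f/√2 = 0.53 SD.

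| Quantity | Gate, then 0.05 | Gate + Bonferroni | Gate + Holm | Gate + Tukey |
|---|---|---|---|---|
| Family-wise error, all arms equal | 0.050 | 0.042 | 0.042 | 0.045 |
| Family-wise error, two arms equal, third 0.53 SD away | 0.050 | 0.017 | 0.032 | 0.019 |
| Power, adjacent pair (evenly spaced) | 0.34 | 0.20 | 0.26 | 0.22 |
| Power, extreme pair (evenly spaced) | 0.80 | 0.76 | 0.77 | 0.77 |
| Power per true pair (one arm different) | 0.73 | 0.62 | 0.65 | 0.64 |
| Both true differences found (one arm different) | 0.65 | 0.47 | 0.53 | 0.49 |

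With two arms equal and the third 0.2 to 5 SD away, the gate followed by 0.05 tests gave a family-wise error of 0.034 to 0.050, and gated Bonferroni gave 0.016 to 0.017. Without the gate, unadjusted pairwise tests gave 0.121 when all arms are equal, so the gate is essential.

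**5. Significant omnibus test, no significant pair.** With equal arms the three squared pairwise t values sum to 3F, and the largest is at least 1.5F. At the critical F this is 1.5 × 3.054 = 4.58. That exceeds 1.975² = 3.90, so some pair is always significant at 0.05. It falls short of 2.420² = 5.86, so under Bonferroni there may be none. The simulated frequency of that outcome was 2.0% (evenly spaced) and 2.9% (one arm different).

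**The case against.** Several objections have force.

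- **The method is left open.** A reader might infer that the plan commits to Bonferroni. It does not: Bonferroni is an example, and the final choice could sit in an analysis plan that is not shown. What stands is that the sentence requires some correction after the gate, and gated Holm and Tukey also give up power in these scenarios, though less.
- **Nothing is invalid.** A reader might infer that the plan gets its error control wrong. It does not. Gated Bonferroni is valid and familiar, and no conclusion of the trial would be false because of it.
- **Bonferroni does lower the error rate.** It would be too strong to say that it gains nothing: family-wise error falls to 0.042 or about 0.017. The supportable claim is that this extra margin is not needed to hold 5% within one outcome.
- **The margin has some use across outcomes.** Three DASS scores, four cognitive domains and global cognition make eight primary outcomes. Suppose two arms are equal on all eight, the third is far away, and the outcomes are independent. The chance of at least one false pairwise claim is then 1 − 0.9835⁸ = 0.12 with gated Bonferroni and 1 − 0.95⁸ = 0.34 without it. Independence is an assumption, and cannot hold exactly because global cognition averages the domains. Correlation lowers both figures. The objection stands as a condition on the change, not as a defence of the second correction: dividing by three pairs was never an across-outcome rule.
- **The simulation is simpler than the analysis.** The plan uses ANCOVA with covariates, multiple imputation with pooled results, and possibly mixed models. The closure argument carries over to adjusted contrasts if the model holds, but control is approximate for pooled tests, and unadjusted pairs rely more on the gate being accurate.

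**Conclusion.** This is a cheap improvement in efficiency, not an error in the plan. Within an outcome, the gate followed by contrasts at 0.05 holds the same 5% level and rejects whenever gated Bonferroni does. At the design effect size, Bonferroni as the second step costs 14 points of power for adjacent pairs, 4 for the extreme pair, 11 per true pair when one arm differs, and 18 for finding both true differences. If QG lies between the other two arms, as the hypotheses suggest, the adjacent-pair figure is the relevant one. Those pairs remain underpowered either way, at 0.34 against 0.20.

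The figures rest on 53 analysed per arm, f = 0.25 on the scale of the analysis, normal errors with common variance, and no covariates or imputation. The closure argument depends on there being exactly three arms and on keeping the gate. A reader might also infer that no multiplicity correction is needed anywhere. The argument does not reach that far, because it says nothing about the several primary outcomes.

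**What to change.** Replace the pairwise clause in Statistical analyses with:

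> After a significant omnibus test at two-sided 0.05 for an outcome, the three pairwise ANCOVA contrasts for that outcome are each tested at two-sided 0.05 (closed test, three arms).

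Keep the gate. If a correction across outcomes is applied, run both the omnibus test and the pairwise contrasts at that outcome's adjusted alpha. The new sentence must not be read as replacing such a correction, so settle the across-outcome rule at the same time.

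The cost is one sentence, with no change to design, sample size or data. There are three downsides. Simultaneous confidence intervals, if wanted, still need an adjusted method. The slack below 5% that Bonferroni gives within an outcome is lost. Control is approximate when tests are pooled over imputations.

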Recent meta-analyses comparing different physical exercise and mind-body approaches have reported their specific effectiveness in improving mental health outcomes among young university populations. Subgroup analyses within these reviews reveal mixed results depending on the type of intervention and the specific mental health issue addressed [10,35–39]. For instance, some studies have reported that exercise-based interventions produce the largest effect sizes in improving depression and anxiety among university students [10,36,39], with one indicating that HIIT outperforms other strategies, including QG and Tai Chi [39]. Another study suggests that aerobic exercise may be more effective in reducing anxiety and stress, while traditional Chinese exercises might be particularly beneficial for managing stress [37]. These reviews highlight the need for direct comparisons between different physical exercise and mind-body interventions to better understand their relative effectiveness in addressing mental health outcomes. Notably, no study has directly compared the effectiveness of physical exercise, traditional Chinese practices, and mindfulness-based strategies. Furthermore, a significant gap exists in research comparing the effects of these interventions on cognitive functions in university students.

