In conclusion, HIFT, MBSR, and QG represent promising well-being strategies. HIFT is an efficient, whole-body physical conditioning modality; MBSR offers a structured and widely accepted method for stress reduction; and QG offers an integrative practice that enhances mind-body harmony. These interventions have demonstrated benefits for psychological well-being and cognitive function in university students. However, to maximize their effectiveness and utilization, it is crucial to investigate the differences and overlap in their effects on various mental health outcomes, as well as to understand their mechanisms of action and the role of individual-level moderators. This can help identify which modality or combination of modalities is most effective in promoting mental well-being during emerging adulthood and may also reveal unique advantages specific to each approach. Furthermore, given their accessibility, cost-effectiveness, and suitability for busy students, these interventions show strong potential to enhance university student well-being, further justifying their study in this context. On the other hand, VR could effectively address issues of low engagement and persistence in training. Given university students’ familiarity with blended learning, they are well-suited for digital mental health support models.

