**Fig 2 pone.0328538.g002:**
[figure not shown]
Key variables of interest in the YoungFitT study. HIFT: High-Intensity Functional Training, MBSR: Mindfulness-Based Stress Reduction Therapy, QG: Qigong, VR: Virtual Reality, HRV: Heart Rate Variability.

The key hypotheses for this objective are: (1) All three interventions will positively affect psychological well-being and cognitive functions at 12 weeks compared to baseline, with each intervention showing a specific profile of outcomes (HIFT: more cognitive gains; MBSR: more psychological gains; QG: moderate benefits in both areas). These positive effects are expected to persist at the 12-week follow-up; (2) All interventions are expected to induce changes in physical components (increased physical activity and fitness status), mental components (enhanced mindful thinking and sleep quality), physiological stress markers (increased HRV), and microbial composition (increased diversity), which will mediate improvements in psychological well-being and cognitive outcomes; (3) Sociodemographic factors (sex and age) and individual factors (cognitive reserve and general intelligence) will moderate changes in outcomes from pre- to post-intervention.

**Study 2 focuses on VR-based physical exercise and mind-body interventions.** The primary objective of this proof-of-concept study is to test the feasibility and preliminary effectiveness of VR-based HIFT, MBSR, and QG interventions on the psychological well-being and cognitive functions of university students. The specific objectives of this study include: (1) Generating virtual environments for HIFT, MBSR, and QG interventions; (2) Evaluating the usability, acceptability, and feasibility of these VR interventions; (3) Studying the effectiveness of VR interventions as depicted in Fig 2; and (4) Exploring the effects and adherence of these VR-based physical exercise and mind-body interventions compared to non-VR interventions.

It is hypothesized that: (1) All VR interventions will positively affect psychological well-being and cognitive functions after 12 weeks, with each intervention displaying distinct outcomes (HIFT: cognitive gains; MBSR: psychological gains; QG: moderate benefits); and (2) VR-based interventions will yield better adherence and greater benefits compared to non-VR interventions.

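### Study 1 compares the arms pairwise only after a significant omnibus test, so the head-to-head question gets no estimate on non-significant outcomes and a selected one elsewhere

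*Protocol article*

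**What the plan says.** Under Statistical analyses, the primary model is an ANCOVA of change scores on group, baseline and covariates, with sex and age always included. The rule for comparing arms follows: "If the omnibus test is significant, we will perform pairwise comparisons within each outcome variable", with a correction for which Bonferroni is the example. The significance level is set by "A two-tailed p-value < 0.05 will denote statistical significance". The stated supplement to the between-group findings is within-group testing (paired t or Wilcoxon). Effect sizes are mentioned once, for Study 2, as partial eta squared.

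The aims are comparative. The Introduction says: "These reviews highlight the need for direct comparisons between different physical exercise and mind-body interventions". It adds, of studying differences and overlap between the interventions: "This can help identify which modality or combination of modalities is most effective". The first Study 1 hypothesis, under Objectives and hypotheses, expects all three interventions to work, "with each intervention showing a specific profile of outcomes": HIFT stronger on cognition, MBSR on psychological outcomes, QG in between on both.

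Under Sample size, the trial is sized for a "one-way ANOVA (fixed effects, omnibus) with three groups": "Assuming a medium effect size (f = 0.25), α = 0.05, and a desired power of 0.80".

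**The concern.** Study 1 has three active arms and no untreated control, so the arm-versus-arm differences are its only randomised effect estimates. A profile across outcomes needs the same contrasts for every outcome, and overlap between arms can be judged only from intervals. The rule produces those contrasts only where the omnibus test is significant.

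Two consequences follow from a literal reading. An outcome with a non-significant test is left with a p-value and three pre-post tests, from which nobody can tell whether the arms are similar or the data too imprecise to say. And the differences that do appear have passed a significance filter, so on average they lie further from zero than the truth wherever two arms really differ.

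This is a point about estimation. It does not dispute the omnibus gate as a test or the choice of correction.

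**Working it through.** **Inputs from the article.** Three arms, 1:1:1; f = 0.25; α = 0.05; power 0.80; required N = 159 (53 per arm); critical F = 3.054; 10% dropout; target 177 (59 per arm).

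**Assumptions.** 53 analysed per arm, equally spaced arm means, differences in units of the residual SD. True differences smaller than f = 0.25 are assumed, not documented.

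**1. The plan's own figure.** One-way ANOVA power uses the noncentral F with 2 and N − 3 degrees of freedom and noncentrality λ = N·f².
- λ = 159 × 0.25² = 9.94; critical F(2, 156) = 3.054; power = 0.805.
- Dropout: 159 / 0.9 = 176.7, rounded up to 177.

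Both figures reproduce. Three further degrees of freedom for baseline, sex and age leave the power at 0.805.

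**2. Chance that an outcome gets no pairwise result.** This is 1 − omnibus power. For equally spaced means with the extreme arms d apart, f = d/√6, so f = 0.25 corresponds to d = 0.25 × 2.449 = 0.61 SD.

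| Extreme-arm difference | f | λ = 159·f² | Omnibus power | No pairwise result |
|---|---|---|---|---|
| 0.61 SD (planned) | 0.25 | 9.94 | 0.805 | 19.5% |
| 0.3 SD (assumed) | 0.122 | 2.39 | 0.258 | 74% |
| 0.2 SD (assumed) | 0.082 | 1.06 | 0.136 | 86% |

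If all 177 supplied data, the planned case would be 15.2% instead of 19.5%.

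**3. Size of the differences that pass the gate.** Three arms of 53 were simulated (600,000 runs per case), and the extreme-arm difference was averaged over the runs with a significant F.

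| True difference | Mean over all runs | Mean given significant F | Ratio to truth |
|---|---|---|---|
| 0.61 SD | 0.61 | 0.68 | 1.10 |
| 0.3 SD | 0.30 | 0.52 | 1.7 |
| 0.2 SD | 0.20 | 0.46 | 2.3 |

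Without the gate the estimate is unbiased. The inflation applies to pairs that truly differ; a truly equal pair stays centred on zero.

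**4. What ungated reporting would give.** The standard error of a pairwise difference is √(2/53) = 0.194 SD, so the 95% interval has a half-width of about 0.38 SD (0.47 SD with Bonferroni for three pairs). An estimate exists for every outcome. Power for the largest pair at f = 0.25 under Bonferroni is 76.7% without the gate and 76.3% with it, so N need not change.

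**The case against.** The strongest reply is that the sentence governs multiplicity-controlled testing and does not say that estimates will be withheld. Which estimates are tabulated is often left to a SAP, and pooling the ANCOVA by Rubin's rules combines group coefficients and standard errors in any case. The mediation, moderation and adherence models carry no gate and may also yield arm contrasts, although their coding is not stated. All this is fair, and it shows that the numbers will exist. But the article fixes a condition on performing the comparisons and nowhere says that differences are reported otherwise. If reporting them is the intent, the fix only makes it explicit.

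The second reply is that the harm is modest at the only effect the article states. That stands: about one outcome in five and 10% inflation. If f = 0.25 is on the unadjusted scale and the covariates correlate 0.5 with the outcome (assumed), these fall to 9% and about 5%.

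Three stronger readings are tempting and are not supported:
- A reader might infer that the reported intervals also lose coverage seriously. That holds for unadjusted intervals at small effects. With the article's example correction, coverage for the extreme pair given a significant F is about 97% at 0.3 SD and 93% at 0.2 SD. At the planned effect it is 97% even unadjusted.
- A reader might multiply the per-outcome chances into a chance that every primary outcome gets an estimate. The number of outcomes depends on whether DASS-21 counts once or three times. They are also not independent, since the global cognitive score averages the domain scores.
- A reader might infer that the authors will call a null result equal effectiveness, or that meta-analysts will receive only inflated differences. The article says neither.

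**Conclusion.** The concern holds as a point about estimation. The gate is a stated rule, it sits badly with the comparative aims, and the article names no ungated between-arm difference to offset it. At the planned f = 0.25 with 53 analysed per arm, the cost is 19.5% of outcomes without a pairwise estimate and inflation of about 1.10. The large figures (74% to 86% without an estimate, 1.7 to 2.3 times inflation) rest on assumed extreme-arm differences of 0.3 to 0.2 SD. Such differences are plausible among three active arms, but the article does not state them. All figures assume that the rule is followed literally and, for the SD conversions, that the arm means are equally spaced. It is worth correcting before analysis. It does not invalidate the planned test.

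**What to change.** Add to the Statistical analyses section, next to the omnibus rule:

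> For every primary outcome, the three adjusted pairwise mean differences with 95% confidence intervals, pooled over imputations, will be reported whatever the omnibus result. The omnibus test and the multiplicity correction govern only which differences may be called statistically significant. A non-significant omnibus test will not be described as equal effectiveness.

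The contrasts come from the ANCOVA already planned. The cost is this short insertion and a somewhat larger results table: three differences per primary outcome, so 18 if DASS-21 counts as one outcome (1 + 4 domains + 1 global = 6) or 24 if it counts as three (8 outcomes). No participants or data are added. The error rate is unchanged, because the gate still controls every claim of significance. The article expects data collection to run until June 2026, so on that timeline the rule can be set before analysis.
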